## Abstract

**Background:**

To describe the rationale and design of an observational cohort study analyzing the effects of endoscopic Totally Extraperitoneal (TEP) hernia repair on male fertility (MAIN study).

**Methods and design:**

The MAIN study is an observational cohort study designed to assess fertility after endoscopic TEP hernia repair. The setting is a high-volume single center hospital, specialized in TEP hernia repair. Male patients of 18-60 years of age, with primary, reducible, bilateral inguinal hernias and no contraindications for endoscopic TEP repair are eligible for inclusion in this study. Patients with an ASA-classification ≥ III and patients with recurrent and/or scrotal hernias and/or a medical history of pelvic surgery and/or radiotherapy, known fertility problems, diabetes and/or other diseases associated with a risk of fertility problems, will be excluded. The primary outcome is the testicular perfusion before and 6 months after TEP hernia repair (assessed by means of a scrotal ultrasonography). Secondary endpoints are the testicular volume (Ultrasound), semen quality and quantity and the endocrinological status, based on serum levels of the sexual hormones follicle-stimulating hormone (FSH), luteinizing hormone (LSH), testosterone and inhibin B before and 6 months after TEP hernia repair.

**Discussion:**

The use of polypropylene mesh is associated with a strong foreign body reaction which could play a role in chronic groin pain development. Since the mesh in (endoscopic) inguinal hernia repair is placed in close contact to the vas deferens and spermatic vessels, the mesh-induced inflammatory reaction could lead to a dysfunction of these structures. Relevant large and prospective clinical studies on the problem are limited. This study will provide a complete assessment of fertility in male patients who undergo simultaneous bilateral endoscopic TEP hernia repair, by analyzing testicular perfusion and volume, semen quantity and quality and endocrinological status before and 6 months after TEP repair.

**Trial registration:**

The MAIN study is registered in the Dutch Trial Register (NTR2208)

## Background

Inguinal hernia repair is one of the most common interventions in general surgery in the Western world. Worldwide over 20 million inguinal hernia repairs are performed annually [1]. The treatment of an inguinal hernia has changed considerably over the past 15 years. Tension-free repair has become the standard surgical technique in inguinal hernia surgery and has led to a considerable reduction in the recurrence rate [2]. Endoscopic Totally Extraperitoneal (TEP) repair is a safe and cost-effective tension-free technique, if expertise is available [3]. Advantages of this method are its low recurrence rate, fast postoperative recovery, low incidence of chronic postoperative pain and high level of patient satisfaction [4-6].

The use of alloplastic material is a complicated issue. The biomaterial most commonly used in hernia repair is polypropylene, which has good mechanical stability and induces an acute inflammatory reaction followed by a chronic foreign body fibroblastic reaction essential for optimal fixation and incorporation of the biomaterial in the abdominal wall [7]. However, the foreign body reaction could also – together with other factors- play a role in chronic pain development. Moreover, as the mesh is placed in close contact with the vas deferens and the spermatic vessels during (endoscopic, preperitoneal) TEP repair, the changes following the mesh-induced fibrotic reaction could lead to a dysfunction of these structures, which might result in fertility problems [8,9].

In 2005, Shin et al. reported on 14 patients with postoperative obstructive azoospermia after hernia repair with implantation of polypropylene meshes [8]. Their report was soon followed by other case reports and studies focusing on this specific problem [10-12]. Patients considered to be at the greatest risk are fertile men (18-60 years of age) undergoing bilateral mesh repair for inguinal hernias and those who undergo an unilateral repair with impairment of the contra-lateral testis [8].

However, a closer look at the existing literature reveals that most studies on obstructive azoospermia are based on animal experiments and incidental case reports. Relevant clinical – and especially large and prospective - studies on the subject, are limited; up until now, only two studies addressed the problem of fertility after endoscopic TEP hernia repair [13,14].

The importance of well-designed clinical trials to study the risk of mesh-associated fertility was therefore pointed out in the guidelines of the European Hernia Society [3].

The aim of this manuscript is to describe the rationale and design of a prospective, observational cohort study evaluating fertility 6 months after endoscopic TEP hernia repair in male patients with bilateral hernias.

## Methods and design

### Study design

The study design is an observational, prospective cohort study involving a high-volume hospital in the Netherlands specialized in the TEP technique for inguinal hernia repair (Diakonessenhuis Utrecht/Zeist). The follow-up of patients is 6 months; parameters of fertility (semen analysis, scrotal ultrasonography and endocrinological status) will be assessed before and 6 months after surgery. A flowchart of the study and the preliminary results (updated until August 15, 2011) is shown in Figure 1. The design, conduct and reporting of this study will adhere to the STROBE guidelines for observational studies [15].

**Figure 1 F1:**
[figure not shown]
Flowchart of the study design and preliminary results.

### Patient population

All male patients of fertile age (i.e. 18-60 years old), with primary, bilateral inguinal hernias, who are scheduled for an elective endoscopic Totally ExtraPeritoneal (TEP) hernia repair are eligible for inclusion in this observational study. A total number of 76 patients will be included in the study. Patients will be recruited during their first visit at the outpatient clinic of the participating hospital. Patients are screened for eligibility according to the criteria listed in Table 1.

**Table 1 T1:** Inclusion and exclusion criteria

**Inclusion criteria**	**Exclusion criteria**
**- Male gender**	**- Female gender**
**- Age ≥ 18 and ≤ 60 years**	**- Age ≥ 60 years**
**- Primary, reducible inguinal hernias**	**- Period of high fever prior to semen analysis**
**- Bilateral hernias**	**- Recurrent inguinal hernias**
**- Eligible for TEP (and therefore for general anesthesia)**	**- Unilateral hernias**
	**- Hydrocele and/or varicocele**
	**- Femoral or scrotal hernias**
	**- Incarcerated hernias**
	**- ASA classification ≥ III**
	**- Previous medical history of:**
	**·Testicular infection(s)**
	**·Testicular torsion**
	**·Cryptorchidism**
	**·Inguinal, scrotal, testicular or prostate surgery**
	**·Vasectomy**
	**·Radiotherapy of pelvic region**
	**·Diabetes Mellitus**
	**·Cystic Fibrosis**
	**·Fertility problems and/or treatment, erection disorders or (other) problems in sexual function**
	**·Use of gonadotrofine medication**
	**·Use of anabolic steroids**

### Intake

The study information is sent to all patients with bilateral hernias after an appointment is made for an initial consultation. The appointment will, ultimately within one week, take place with one of the four surgeons and the investigator at the outpatient clinic. After screening for eligibility criteria, informed consent is obtained and the patient is included in the study. Preoperative patient data are obtained by the investigator (Table 2) and are – as standard procedure - recorded in the patient Electronic Patient Chart (Dutch: EPD)

**Table 2 T2:** Preoperative data

**- Age**
**- ASA-classification**
**- Co-morbidity **(see Table 1)
**- Medication**
**- Smoking habit**
**- Body Mass Index (BMI)**
**- Numerical Rating Scale (NRS) to evaluate pain associated with the inguinal hernia**
**- Duration of (hernia associated) symptoms in months**

### Interventions

The perioperative care and surgical technique are not different for patients participating in this trial compared to patients who are not. The applied surgical method is the simultaneous bilateral endoscopic TEP inguinal hernia repair, using a “double-mesh” implantation technique performed under general anesthesia. Two identical polypropylene meshes (Prolene, 12x15 cm) are positioned in a tension-free manner in the preperitoneal space, as described previously [5]. The mesh graft is not fixed, since it reduces operative time, saves costs and avoids possible entrapment neuralgia. Hernia types are classified during TEP repair according to the Nyhus classification. Intra-operative complications and operative time are registered in the Electronic Patient Chart (Dutch: EPD).

Fertility aspects are evaluated by means of scrotal ultrasonography, semen analysis and assessment of the endocrinological status, based on serum levels of the sexual hormones follicle-stimulating hormone (FSH), luteinizing hormone (LSH), testosterone and inhibin B.

A scrotal ultrasonography is performed to investigate bilateral testicular volume and to detect possible signs of distension of the epididymis and/or vas deferens [16].

The flow in the testicular artery is measured by Doppler ultrasonography measuring the blood flow velocity (cm/s) in the testicular, capsular and intratesticular arteries. The parameters that are to be evaluated are described in the Additional file 1 Addendum A. Scrotal ultrasound is performed by one experienced radiologist.

Semen analysis is done in a standardized manner. Classic parameters, such as seminal volume (mL), sperm concentration (10^6^ cells/mL), motility (% progression) and morphology (% normal) are analyzed. Patients are instructed about minimal (2 days) and maximal (7 days) abstinence so that reliable semen samples can be obtained.

Fertility aspects are evaluated preoperatively (on the day of surgery) and 6 months postoperatively.

### Postoperative management and follow-up

Patients are discharged on the day of surgery, unless complications occur. Duration of hospital stay and postoperative complications are registered in the EPD. At discharge, patients are advised to take pain medication (Paracetamol and if necessary Diclofenac) when necessary and avoid strenuous physical activity (lifting, sports) during the first postoperative week. There are no other (physical) restrictions. Patients undergo a (physical) examination 6 weeks and 6 months after surgery. Surgery related complications, the time that it takes to restart normal activities pain status, evaluated by the Numerical Rating Scale (NRS) and the presence of recurrent hernias are evaluated by an experienced surgeon. The 6 monthly visit to the outpatient clinic is combined with the assessment of fertility aspects (see “*Intervention”*).

### End-points

The primary endpoint is the testicular perfusion before and 6 months after endoscopic TEP hernia repair, as measured by Doppler ultrasonography.

Secondary endpoints are the testicular volume, semen quality and quantity and serum levels of sexual hormones (FSH, LH, testosterone and inhibin B), evaluated before and 6 months after endoscopic TEP hernia repair.

### Safety measures

All four surgeons have extensive experience with TEP repair (over 500 procedures per surgeon). Standard safety measures are applied at all times. The operation and perioperative care are not different for patients participating in this study compared to patients who do not participate. Therefore, serious adverse events (SAE), other than SAE’s that might eventually occur following endoscopic TEP repair (hemolytic shock, bladder or bowel laceration) are not expected to occur in this study.

### Sample size and power

Since insufficient human data are available in the current literature regarding fertility aspects (scrotal ultrasound data, semen characteristics) after inguinal hernia repair in men, no adequate power analysis, and consequently no adequate sample size calculation, can be performed.

However, in two studies regarding testicular perfusion after endoscopic TEP hernia repair, a difference was found in the end diastolic velocity (EDV) of the a. testicularis (as a parameter of testicular perfusion). The follow-up was respectively 7 days and 3 months after TEP hernia repair; mean differences (δ) of respectively 0.1 cm/s and 1.1 cm/s were observed in the EDV of the a. testicularis [17,18].

Based on these findings, an assumption is made that, if the testicular perfusion 6 months after TEP repair is compared with the perfusion preoperatively and a δ of 0.4 cm/s is detected in the EDV of the a. testicularis, 76 patients have to be included in this study with a two sided alpha of 0.05 and a power of 0.90. In this calculation, a loss to follow-up of 15% is expected.

### Statistical methods

SPSS software (SPSS, Chicago, Illinois, USA) will be used for statistical analysis. Normality of continuous data will be evaluated with the Shapiro Wilk test. Homogeneity of variances will be checked by means of Levene’s analysis. Differences in preoperative and postoperative fertility parameters will be analyzed by means of a paired sample *T*-test (parametric data) or a Wilcoxon signed-ranked test (non-parametric data). Data will be compared to the age-adjusted reference values in the literature. Testicular volume and perfusion will be evaluated for both testes separately. Significance is set at a level of p ≤ 0.05 (two-sided).

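### The tests stated for semen have almost no power if azoospermia affects only a few men, and the article fixes no per-man semen outcome

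*Protocol article*

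**What the plan says.** All from the protocol article.

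- **Motive (Background).** The clinical case opens with a series that "reported on 14 patients with postoperative obstructive azoospermia after hernia repair with implantation of polypropylene meshes". The article gives no denominator or incidence. The wider rationale covers both the vas deferens and the spermatic vessels: "the changes following the mesh-induced fibrotic reaction could lead to a dysfunction of these structures, which might result in fertility problems". Fertile men having bilateral mesh repair are named among those at greatest risk, and the eligibility criteria select that group.
- **Endpoints (End-points).** "The primary endpoint is the testicular perfusion before and 6 months after endoscopic TEP hernia repair, as measured by Doppler ultrasonography". Semen comes next: "Secondary endpoints are the testicular volume, semen quality and quantity and serum levels of sexual hormones".
- **Measurements (Interventions).** "Classic parameters, such as seminal volume (mL), sperm concentration (10^6^ cells/mL), motility (% progression) and morphology (% normal) are analyzed". Scrotal ultrasound is also used "to detect possible signs of distension of the epididymis and/or vas deferens".
- **Analysis (Statistical methods).** "Differences in preoperative and postoperative fertility parameters will be analyzed by means of a paired sample" t-test for parametric data, or a Wilcoxon signed-rank test otherwise. Then: "Data will be compared to the age-adjusted reference values in the literature". The unit of that comparison and the cut-off are not given.

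**The concern.** Both stated tests look for a shift across the whole group. That suits a graded effect on perfusion, hormones or sperm output in most men. It does not suit an effect in which a few men lose all sperm and the others do not change, because those few are lost in the ordinary sample-to-sample variation of the rest.

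The reference-value sentence does not clearly fill the gap. Read at group level, it could leave the cohort looking normal after real losses in individual men, since men with known fertility problems, vasectomy, varicocele or cryptorchidism are excluded at entry. Read per man, it would help, but no limit is named.

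The Discussion promises a complete assessment of fertility and says that small numbers have so far prevented firm conclusions. A non-significant paired test on semen could be taken as reassurance about azoospermia that it cannot give.

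**Working it through.** **1. Number of men.** Sample size and power states 76 patients, a difference of 0.4 cm/s in end diastolic velocity, two-sided alpha 0.05, power 0.90 and 15% loss. The SD of the paired difference is not stated, so 76 can only be solved backwards from n = (SD × (1.960 + 1.282) / 0.4)².

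- SD 0.98 gives 63.1, so n = 64, and 64 / 0.85 = 75.3, so 76.
- SD 1.00 gives 65.7, so n = 66. Then 66 / 0.85 = 77.6, so 78, while 66 × 1.15 = 75.9, so 76.

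The figure is therefore consistent with an SD near 0.98 to 1.00. It concerns perfusion, not semen, and is used here only for the evaluable number: 76 × 0.85 = 64.6, taken as 64. The article says no adequate power analysis is possible for semen characteristics.

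**2. Power of the stated tests when k of 64 men become azoospermic.** The article gives no semen distribution, so these are assumptions: lognormal concentration, k postoperative values set to zero, and no systematic change in the other men. Setting A has a median of 50 × 10⁶/mL, with log-SD 0.8 between men and 0.4 within. Setting B has a median of 60, log-SD 0.7 between men, and 0.3 or 0.5 within. Each test is two-sided at 0.05. Entries are the share of simulated trials that reject; ranges in the B columns run over the two within-man SDs.

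| k (share of 64) | A: t-test | A: Wilcoxon | B: t-test | B: Wilcoxon |
|---|---|---|---|---|
| 0 | 4% | 5% | 3–5% | 4–5% |
| 3 (4.7%) | 6% | 6% | 5–7% | 7% |
| 5 (7.8%) | – | – | 9–14% | 10–12% |
| 6 (9.4%) | 13% | 14–15% | 11–18% | 13–16% |
| 8 (12.5%) | – | – | 16–30% | 22–27% |
| 13 (20%) | – | – | 36–64% | 47–61% |

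Across all runs, k = 3 gives about 5 to 8%, close to the false-positive rate. For k = 6 most results lie between 11 and 16%; the 18% is the t-test with the smallest within-man SD (0.3).

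**3. What a per-man count would give with 64 men.** Exact (Clopper-Pearson) 95% limits:

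- 0 cases: upper limit 1 − 0.025^(1/64) = 5.6%. The one-sided 95% bound is 1 − 0.05^(1/64) = 4.6%.
- 1 case: 0.04 to 8.4%.
- 3 cases: 1.0 to 13.1%.
- 6 cases: 3.5 to 19.3%.

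The chance of seeing at least one case is 1 − (1 − p)^64: 47% at an assumed true risk of 1%, 73% at 2%, 86% at 3% and 96% at 5%.

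**4. Limit of a McNemar test.** If all k shifts go one way, the exact two-sided p-value is 2 × 0.5^k: 0.25 for k = 3, 0.063 for k = 5 and 0.031 for k = 6. At least 6 one-way shifts are needed for significance, so the count and its interval carry the information, not the p-value.

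**The case against.** Several objections stand and limit the point.

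- A reader might infer that the plan compares pre and post averages only. It does not: the Wilcoxon alternative is not a test of means, and the same section adds a reference-value comparison, which could be meant per man.
- A reader might infer that the study cannot detect azoospermia. Every man has a sperm concentration measured before surgery and at 6 months, so a man who falls to zero is visible in the data. The article does not say that such results would go unreported.
- A reader might take azoospermia as the sole motive. Vascular damage is the other, perfusion is the primary endpoint, and paired tests suit graded effects.
- The article does not say that the harm is all-or-none or confined to a minority. That pattern, and the simulated distributions, are assumed. If 13 of 64 men were affected, power would be 36 to 64%.
- The article condenses a fuller protocol, and an additional file lists the Doppler parameters. Per-man summaries or the handling of distension may be set out there. Their absence from the article is not proof of omission.

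What remains is that the article does fix a test for semen, and that test fits one of its leading motives poorly. This is a matter of method and not only of missing detail.

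**Conclusion.** The point holds in limited form. For semen, the only stated test is of overall pre-post shift, alongside a reference comparison of undefined unit and cut-off. If about 5% of men became azoospermic and the rest were unchanged, that test would very probably return a non-significant result, at little more than its false-positive rate; at about 9% of men it would still miss the effect in more than four trials out of five. The exact sizes rest on assumed lognormal concentrations and 64 evaluable men, but the conclusion was the same in every setting tried. It weakens as more men are affected. It concerns a secondary endpoint and leaves the perfusion analysis untouched. The change should be made, but the point does not threaten the study's primary result.

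**What to change.** Keep the paired tests. Add to the Statistical methods, before analysis:

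1. As a prespecified secondary semen analysis, the number of men with sperm at baseline who are azoospermic at 6 months, out of those with both samples, with an exact 95% CI.
2. The reference values applied per man, as a named cut-off, with the number of men moving from at or above the limit to below it and the reverse, compared by McNemar's test.
3. The number of men with new epididymal or vas distension on ultrasound at 6 months.
4. A statement that a non-significant paired test does not exclude azoospermia in a few men, and that zero cases in about 64 men excludes only risks above about 5.6% (two-sided 95% limit).

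The measurements are already planned, and 21 of 76 men had been included at the date the article gives, so this needs only a few lines of text. The cost is one or two extra secondary analyses with wide intervals. A rare harm would remain unresolved at this sample size, but the report would say so openly.

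### The primary endpoint is not tied to one variable and is tested in each testis separately, while the sample size covers a single comparison

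*Protocol article*

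**What the plan says.** Four places in the protocol article bear on this point.

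- **End-points:** "The primary endpoint is the testicular perfusion before and 6 months after endoscopic TEP hernia repair, as measured by Doppler ultrasonography". No artery, Doppler parameter or side is named.
- **Interventions:** Doppler is used for "measuring the blood flow velocity (cm/s) in the testicular, capsular and intratesticular arteries". The list of parameters is elsewhere: "The parameters that are to be evaluated are described in the Additional file 1 Addendum A". That addendum is not among the documents reviewed. The same section says that every man has simultaneous bilateral repair with two identical meshes.
- **Sample size and power:** the calculation supposes that "a δ of 0.4 cm/s is detected in the EDV of the a. testicularis" and concludes that "76 patients have to be included in this study with a two sided alpha of 0.05 and a power of 0.90", allowing 15% loss to follow-up. It describes EDV as a parameter of perfusion, names no side and gives no SD.
- **Statistical methods:** before and after values are compared by paired t-test or Wilcoxon signed-rank test at a general two-sided level of 0.05. On laterality: "Testicular volume and perfusion will be evaluated for both testes separately".

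**The concern.** The sample size describes one test. The endpoint and analysis text describe at least two, because perfusion is assessed in the left and the right testis separately. The article does not say what the study concludes if one side is significant and the other is not, so the stated alpha of 0.05 and power of 0.90 belong to no defined primary decision.

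Separate analysis is a stated choice, not a detail left open, and it fits this design poorly. Unilateral hernias are excluded, so there is no untreated side to act as a control. Both testes receive the same type of repair, and the question concerns the man's fertility. Unless the changes in the two testes are perfectly correlated, analysing the sides apart also gives up precision that the data already contain.

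**Working it through.** **Inputs from the article.** Difference 0.4 cm/s; two-sided alpha 0.05; power 0.90; 76 enrolled; 15% loss. Evaluable men: 76 × 0.85 = 64.6, taken as 64.

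**Inputs assumed.** The SD of the paired change (not stated) and the correlation between a man's two testes (not stated).

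**1. The plan's own figure.** For a paired comparison, n = ((1.960 + 1.282) × SD / 0.4)². Without an SD, 76 cannot be reproduced, but it can be solved backwards. With n = 64, SD = 0.4 × √64 / 3.242 = 0.99 by the normal formula, or 0.97 by the noncentral t. In the forward direction, SD 0.98 gives 64 evaluable and 64 / 0.85 = 76 enrolled. SD 1.0 gives 66 evaluable, which is 76 if inflated as 66 × 1.15 and 78 if inflated as 66 / 0.85. The plan therefore implies an SD of about 0.97–1.00 for one comparison. I use 1.0 below; one side tested alone then has power 0.88 with 64 men.

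**2. Number of primary tests.** Taking testicular-artery EDV as the primary measure, there are two (left and right). If all three arteries also counted as primary, there would be 3 × 2 = 6, before any further Doppler parameter. The article does not state the latter.

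**3. False-positive risk if any one significant test counts.** Independent tests: 1 − 0.95² = 0.098 and 1 − 0.95⁶ = 0.265. Correlated tests were simulated with equal pairwise correlation:

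| Correlation | 2 tests | 6 tests |
|---|---|---|
| 0 | 9.8% | 26.5% |
| 0.5 | 9.0% | 20.7% |
| 0.8 | 7.8% | 13.9% |

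**4. Power for a true 0.4 cm/s effect on both sides** (64 men, SD 1.0). The either, both and disagreement rows are simulated; the mean row is noncentral t, with SD of the mean = 1.0 × √((1 + ρ)/2), that is 0.866 and 0.922.

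| Rule | ρ = 0.5 | ρ = 0.7 |
|---|---|---|
| Either side significant | 0.96 | 0.94 |
| Both sides significant | 0.81 | 0.82 |
| Exactly one side significant | 0.15 | 0.12 |
| One test on the mean of both testes | 0.95 | 0.93 |

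The first two rows are alternatives. The either-side rule has the alpha problem of step 3 but no power problem. The both-sides rule has a joint false-positive rate of only about 1–2% at these correlations, but it falls short on power.

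**5. What averaging costs.** With 0.4 cm/s on one side and none on the other, the mean shifts by 0.4 / 2 = 0.2 cm/s. Power on the mean is then 0.44 (ρ = 0.5) or 0.40 (ρ = 0.7), against 0.88 for the affected side tested alone.

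**The case against.** A reader might infer that the plan makes six or more primary tests and that any one of them would count as a positive study, with a false-positive risk of up to 26%. The article supports neither step. It lists three arteries as places where velocity is measured, without calling each a primary test, and the addendum that might rank the parameters is not shown. The only perfusion measure tied to an alpha is the EDV of the testicular artery. No any-one-wins rule is written, and if both sides had to be significant there would be no inflation. Two tests is the only certain count, and the 14–26% range is conditional.

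Multiplicity rules are also often left to a fuller document, so silence on them in an article is not itself a fault. That is fair. What remains is in the text: a broad endpoint, an explicit choice to evaluate each testis separately, and a calculation for one comparison.

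Per-testis reporting also has merit. Hernia type is classified at operation and may differ by side, and step 5 shows that averaging loses much of the power for a one-sided effect. This is a reason to keep the side-specific results as planned secondary analyses. It does not justify leaving the primary decision undefined.

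Finally, this is an uncontrolled cohort whose article concedes that an adequate power analysis was not possible. That limits the severity of the point.

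**Conclusion.** The point holds, as something that should be fixed. The primary endpoint is not tied to one variable, and there are at least two primary tests where the sample size allows for one. Neither simple decision rule keeps both stated properties:

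- **Either side suffices:** false-positive risk about 8–10% (14–26% if six tests counted), power about 0.94–0.96.
- **Both sides required:** alpha controlled, power about 0.81–0.82, below 0.90.

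Even with a real 0.4 cm/s effect on both sides, left and right would disagree on significance in about 12–15% of studies, and the article does not say what would then be concluded.

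These sizes rest on an SD of change of 1.0 cm/s, 64 evaluable men, and between-side correlations of 0.5–0.7 for power and 0–0.8 for alpha. The SD is consistent with the planned 76 patients; the correlations are pure assumptions.

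**What to change.** In End-points and Statistical methods, name one primary variable: the 6-month change in EDV of the testicular artery, which the sample size already uses. Analyse it once per man at two-sided 0.05, either as the mean of the two testes or in a mixed model with a random patient effect. Under the assumptions above, power is about 0.93–0.95 with the planned numbers.

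List the left and right results, the capsular and intratesticular arteries and the other Doppler parameters as pre-specified secondary results. Treat testicular volume the same way, with the patient mean first and the sides second. State the SD behind the 76 patients.

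The change is to wording only and needs no new measurements or patients. It should be dated and made before the outcome data are analysed. The cost to disclose is that the primary test is weak against a purely one-sided effect (power about 0.40–0.44 for 0.4 cm/s, against about 0.88 for that side alone), which would be picked up mainly in the side-specific secondary results.
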